Conventional treatment approaches include aerobic exercise and cognitive behavioral therapy. These involve activities such as brisk walking, jogging, cycling, and engaging in cognitive skill exercises or workbooks. Studies have shown that, in addition to medical treatment, combining cognitive and aerobic exercises helps reduce symptoms of cognitive impairment without causing complications. Therefore, such interventions should be recommended for all patients with cancer experiencing CICI.

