### Control Group

Participants will perform aerobic exercises and cognitive behavioral training daily. The program will include brisk walking, cycling, jogging, and cognitive skill activities for 45 minutes per day, 5 days a week, over 4 weeks. These activities will not require direct supervision.

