### Intervention Group

Domain-specific cognitive exercises to be administered to patients are outlined in Table 2.

**Table 2 table2:** Intervention group.

Problem identified		Physiotherapy intervention	Dosage		

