**Physical fitness**					
	Aerobic exercises [18] (frequency, intensity, interval, and time principle)	Brisk walking, jogging, and static cycling	Frequency: 5-6 times per week; intensity: easy to moderate, approximately 60%-75% of maximum heart rate.		

^a^N/A: not applicable.

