### Statistical Analysis

For demographic factors, all data will be summarized using baseline characteristics, expressed as the mean and SD for continuous data and as frequency and percentage for categorical data.

The analysis of outcome variables will primarily focus on continuous variables. For parametric data, the minimum, maximum, mean, SD, SE, and 95% CI will be summarized. The normality of continuous outcome variables will first be tested using the Kolmogorov-Smirnov test at a 5% level of significance (*P*≤.05). If the data are found to deviate from normality, a nonparametric test will be applied to determine significance. An independent *t* test will be conducted for group comparisons to assess significant differences at the 5% level (*P*≤.05). The intervention groups will receive (1) cognitive training supplementing traditional physical treatment and (2) traditional physical treatment.

The effect size at different assessment visits between the 2 groups will be calculated for the variables MMSE and Montreal Cognitive Assessment. For nonnormal data, descriptive statistics will include the mean, median, and lower and upper quartiles. The Mann-Whitney test will be applied to determine statistical significance when nonparametric methods are required.

Categorical variables will be summarized using frequency (n) and percentage. Chi-square analysis will be performed to evaluate efficacy across categorical variables. An intention-to-treat analysis will be applied to minimize attrition bias among participants, including those lost to follow-up or deceased due to adverse effects of chemotherapeutic drugs.

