## Discussion

### Anticipated Findings

This study will evaluate and compare the effects of cognitive rehabilitation and conventional therapy on cognition in patients with CICI. It is anticipated that this framework will significantly enhance the cognitive functions of patients receiving cognitive therapy as an intervention alongside conventional management protocols.

We hypothesize that cognitive training will result in measurable changes in brain magnetic resonance imaging, including improved perfusion, enhanced white matter connectivity (particularly involving the hippocampus), and increased brain volume (including the hippocampus). We have designed a randomized controlled trial (RCT) to investigate the effects of cognitive training and physical exercise on cognitive functioning in patients with cancer who have undergone chemotherapy and reported cognitive difficulties confirmed by standardized and validated neuropsychological assessments. Several underlying mechanisms may explain the effectiveness of the therapies included in this study. Cognitive rehabilitation and active exercises (such as weight training, aerobic training, dance, and yoga) may enhance physical capacity by counteracting reduced activity levels during or after cancer treatment [23]. Furthermore, increased physical activity can positively influence mental health. Psychosocial therapies promote activity management and stress coping, thereby reducing fatigue. Cognitive rehabilitation enhances neuroplasticity, enabling the brain to reorganize and adapt in response to injury, and helps develop compensatory strategies that allow individuals to manage cognitive deficits more effectively. It also contributes to building cognitive reserve, thereby reducing the risk of cognitive decline and promoting resilience. Several RCTs have demonstrated the efficacy of cognitive rehabilitation in improving cognitive function and quality of life, as well as in reducing symptoms of anxiety and depression in individuals with CICI [24]. Meta-analyses have further shown that cognitive rehabilitation is associated with significant improvements in cognitive function, particularly in attention and memory [25].

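### The analysis section describes an add-on comparison, but the arms as specified are two different packages, so a between-arm difference cannot be credited to adding cognitive training alone

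*Protocol article*

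**What the plan says.** All places are in the protocol article.

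- **Statistical Analysis** names the two groups as "1) cognitive training supplementing traditional physical treatment and (2) traditional physical treatment".
- **Anticipated Findings** opens by saying the study compares cognitive rehabilitation with conventional therapy, then expects benefit from "cognitive therapy as an intervention alongside conventional management protocols".
- **Objectives**, second item, sets cognitive rehabilitation against conventional therapy.
- **Background** describes the conventional option: "Conventional treatment approaches include aerobic exercise and cognitive behavioral therapy".
- **Control Group**: "Participants will perform aerobic exercises and cognitive behavioral training daily". The programme combines walking, cycling and jogging with "cognitive skill activities for 45 minutes per day, 5 days a week, over 4 weeks", and adds: "These activities will not require direct supervision".
- **Rationale** explains why cognitive behavioral training was put in the control arm, so its presence there is deliberate.
- **Intervention Group**: "Domain-specific cognitive exercises to be administered to patients are outlined in Table 2". Table 2 lists memory, executive function, attention and information-processing tasks, and an aerobic row ("Brisk walking, jogging, and static cycling"). Cognitive behavioral training does not appear in it.
- **Abstract, Conclusions** credits the expected improvement in cognition to the cognitive therapy.

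**The concern.** An add-on trial supports a simple inference. Both arms share a background treatment, so a difference between them is the effect of what was added. The Statistical Analysis section and part of Anticipated Findings promise that design.

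The arm descriptions point to a substitution instead: one active cognitive component in the intervention arm and a different one in the control arm. If so, a positive result does not show that adding cognitive training to conventional treatment helps. Nor does a null result show that cognitive training does nothing, since the comparator was itself chosen as an active treatment. Every between-group test rests on this contrast, so the article should state it in one way only.

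**Working it through.** The point turns on text rather than arithmetic. The plan's own sample size is not in dispute: 2 × (7.84/0.64) + 0.96 = 25.46, rounded up to 26 per group, and 26 + 4 = 30 with the dropout allowance.

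**Step 1. Components by arm, as specified.**

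| Component | Control (Control Group section) | Intervention (Table 2) |
|---|---|---|
| Aerobic exercise | Yes, in a 45-minute programme 5 days a week | Yes, 5-6 times per week at 60%-75% of maximum heart rate |
| Domain-specific cognitive exercises | Not listed | Yes |
| Cognitive behavioral training | Yes | Not listed |
| Cognitive skill activities | Yes | Not listed under that name |
| Therapist role | Direct supervision not required | Several tasks run or observed by a therapist (word association, Stroop task, the Perform step) |

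The add-on wording allows one row to differ. As written, the arms differ in the domain-specific exercises and in the cognitive behavioral training and cognitive skill activities. They apparently also differ in therapist contact, and the aerobic schedule is stated differently.

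**Step 2. Can any reading of the add-on wording fit both arms?** It depends on what traditional physical treatment means.

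- *Aerobic exercise only.* Table 2 then fits the first group (cognitive tasks plus aerobic exercise). The Control Group section does not fit the second, because it adds cognitive behavioral training and cognitive skill activities.
- *The conventional treatment of the Background section* (aerobic exercise plus cognitive behavioral therapy). The Control Group section then fits the second group. Table 2 does not fit the first, because it omits the cognitive behavioral part.
- *Cognitive behavioral training delivered as the cognitive skill activities.* The Background section can be read this way. The trial then compares one kind of cognitive activity with another on an aerobic background, which is a substitution and still not an add-on.

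Each reading leaves at least one arm that does not match.

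**Step 3. What the difference estimates.** Assume for illustration that component effects add up. Let D be the domain-specific exercises, B the control arm's cognitive components, T therapist contact (inferred) and A the aerobic part.

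- Add-on contrast: (A + D) − A = D.
- Arms as specified: (A₁ + D + T) − (A₀ + B) = D − B + T + (A₁ − A₀).

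B and T enter with opposite signs and the documents give no value for either. The net departure from D therefore has no known size or direction.

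**The case against.** The strongest reply is that the trial is already a head-to-head study. Objective 2 says so, as does the first sentence of Anticipated Findings. The Rationale defends an active comparator, and randomisation supports a comparison of packages however many parts they contain. On this view only the control label in the Statistical Analysis section is incomplete. Most of this stands: the package contrast is valid and estimable, and a multi-component comparator is a legitimate choice. It does not remove the conflict, because the add-on wording appears in two places and the anticipated conclusion relies on it.

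Several stronger readings are tempting but unsupported.

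- *That no conclusion can be drawn.* A reader might infer this from the mismatch. Only the add-on conclusion, and attribution to cognitive training alone, fail.
- *That one arm is supervised and the other is not.* No sentence says the intervention arm is supervised; this is inferred from the therapist-run tasks. For control, the text says only that direct supervision is not required.
- *That the active control undermines the power calculation.* The effect size of 0.8 is an estimate for the two trial arms. Nothing says it was set against a control without cognitive behavioral training, so there is no basis for reducing it.
- *That the intervention arm gets more treatment time.* Table 2 does not say that every task is done in every session, so its doses cannot be summed and set against the control arm's 45 minutes.

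It is also possible that both arms were meant to receive cognitive behavioral training. That would rescue the add-on wording, but Table 2 does not list it, so the text would still need correcting.

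**Conclusion.** The inconsistency is real and lies in the current text. The article states two incompatible contrasts, and the arms as specified match the head-to-head one. A between-arm difference will describe therapist-involved domain-specific cognitive exercises plus aerobic exercise against aerobic exercise plus cognitive behavioral training and cognitive skill activities. It cannot be attributed to adding cognitive training alone.

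The size of the problem is qualitative: two differences in listed content where the add-on wording allows one, plus an inferred difference in therapist contact and a differently stated aerobic schedule. This rests on taking the Control Group section and Table 2 as complete descriptions of the arms. The between-group tests and the sample size of 30 per group are unaffected. It should be fixed before results are interpreted, but it does not invalidate the design.

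**What to change.** Reconcile Background, Objectives, Control Group, Intervention Group with Table 2, Rationale, Statistical Analysis and Anticipated Findings into one statement of what each arm receives and which contrast the trial estimates. Which components and schedules belong in each arm is for the investigators to decide.

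If the arms stay as in the Control Group section and Table 2:

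1. Replace the add-on wording in Statistical Analysis and Anticipated Findings with a head-to-head statement of the two packages.
2. Limit the conclusion, including the one in the abstract, to that package contrast.

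If an add-on design was intended, the arm descriptions must be corrected to show the shared treatment in both arms.

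The first route costs only wording. Its downside is a narrower claim: the trial could say which package did better, but not which component was responsible.

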### Monitoring Methods

#### Data Monitoring

The Data Monitoring Committee of Ravi Nair Physiotherapy College will be responsible for overseeing and monitoring the study data.

#### Monitoring Harms

Every instance of an adverse event will be reported to the Ethics Committee and the clinician responsible for evaluating and managing both anticipated and unanticipated adverse events, as well as any other unforeseen consequences arising from the trial interventions or trial conduct.

## Results

As of November 9, 2024, we enrolled 60 participants. Data collection will occur from November 14, 2024, to November 14, 2025. We expect the results on the effects of cognitive rehabilitation on cognition and quality of life in patients with CICI to be significant, with the findings scheduled for publication on November 25, 2025.

## Discussion

### Anticipated Findings

This study will evaluate and compare the effects of cognitive rehabilitation and conventional therapy on cognition in patients with CICI. It is anticipated that this framework will significantly enhance the cognitive functions of patients receiving cognitive therapy as an intervention alongside conventional management protocols.

We hypothesize that cognitive training will result in measurable changes in brain magnetic resonance imaging, including improved perfusion, enhanced white matter connectivity (particularly involving the hippocampus), and increased brain volume (including the hippocampus). We have designed a randomized controlled trial (RCT) to investigate the effects of cognitive training and physical exercise on cognitive functioning in patients with cancer who have undergone chemotherapy and reported cognitive difficulties confirmed by standardized and validated neuropsychological assessments. Several underlying mechanisms may explain the effectiveness of the therapies included in this study. Cognitive rehabilitation and active exercises (such as weight training, aerobic training, dance, and yoga) may enhance physical capacity by counteracting reduced activity levels during or after cancer treatment [23]. Furthermore, increased physical activity can positively influence mental health. Psychosocial therapies promote activity management and stress coping, thereby reducing fatigue. Cognitive rehabilitation enhances neuroplasticity, enabling the brain to reorganize and adapt in response to injury, and helps develop compensatory strategies that allow individuals to manage cognitive deficits more effectively. It also contributes to building cognitive reserve, thereby reducing the risk of cognitive decline and promoting resilience. Several RCTs have demonstrated the efficacy of cognitive rehabilitation in improving cognitive function and quality of life, as well as in reducing symptoms of anxiety and depression in individuals with CICI [24]. Meta-analyses have further shown that cognitive rehabilitation is associated with significant improvements in cognitive function, particularly in attention and memory [25].

A systematic review examined the effects of interventions aimed at enhancing cognitive function in patients experiencing CRCI. Studies involving patients with metastatic cancer or preexisting cognitive deficits were excluded. The review included studies published between January 2011 and September 2022. Various interventions were identified for managing CRCI, and the outcome measures were found to be consistent across studies [26]. An RCT focusing on patients with cancer with CICIs also highlighted cognitive rehabilitation as an effective approach to address the cognitive deficits commonly observed following chemotherapy [18]. According to research, the majority of BC survivors, particularly those who have undergone chemotherapy, experience long-term cognitive abnormalities that significantly diminish their quality of life [27]. Executive functions—including working memory, cognitive flexibility, multitasking, planning, and attention—are among the most severely affected cognitive domains. Previous studies across various populations have shown that cognitive training, a behavioral approach used to address cognitive deficits, can lead to notable improvements in specific cognitive abilities such as executive functions. Kiesl et al [24] conducted an RCT to evaluate the effectiveness of cognitive training through a 12-week program and concluded that it resulted in significant improvements in processing speed, planning, and task performance. A study by Ferguson et al [28] evaluated the efficacy of cognitive behavioral therapy and memory and attention adaptation training (MAAT), both designed to improve cognitive function in patients with cancer. Following treatment, they concluded that cognitive behavioral therapy was more effective than MAAT; however, patients reported higher satisfaction with MAAT [29]. A systematic review by Peng et al [30] suggested that exercise interventions improve cognitive function and quality of life, as assessed through self-reported outcomes, and emphasized the need for higher-quality research to further explore exercise strategies in CRCI. Similarly, a systematic review by Hilfiker et al [20] assessed physiotherapeutic interventions for CRCI following cancer treatment and concluded that physiotherapy, including cognitive rehabilitation, was effective and led to significant improvements in cognition and quality of life.

An RCT investigated the feasibility and preliminary effectiveness of a novel online executive function training program for long-term BC survivors. Forty-one BC survivors (21 active and 20 waitlist) completed the 48-session training program over 12 weeks. The cognitive training resulted in significant improvements in cognitive flexibility, verbal fluency, and processing speed, with marginally significant downstream improvements in verbal memory as assessed using standardized measures [31]. According to Pendergrass et al [32], cognitive rehabilitation and training methods incorporating adaptive challenge levels, awareness practice, and repetitive skills training had a positive effect on cognitive function and self-reported quality of life. Similarly, a study by Wongarsa et al [33] on integrated interventions for mild cognitive impairment in older adults demonstrated that brain training activities—such as word guessing and memorization, image classification, music-based responses, basic arithmetic computation, and step-by-step recipe writing and cooking—greatly enhanced processing speed, attention, and memory. A systematic review by Melillo et al [34] encompassing studies conducted worldwide illustrated various approaches to managing cognitive impairment. Bellens et al [7] investigated the effects of web-based cognitive training, while in Canada (2018 and 2022), Campbell et al [35] and Duval et al [36] examined the impact of aerobic exercise on cognitive functions. Another study focused on the use of mindfulness-based stress reduction as an intervention [25].

### Strength

According to a consensus statement from the International Multidisciplinary Roundtable, cancer survivors can safely engage in sufficient exercise training to improve physical fitness, restore physical functioning, enhance quality of life, and reduce cancer-related fatigue. However, uncertainty remains regarding the effects of exercise on various outcomes, including peripheral neuropathy and cognitive functioning. The statement concluded that insufficient research exists on several aspects, such as anxiety, depressive symptoms, fatigue, health-related quality of life, cognitive decline, physical function, and the safety of exercise training for individuals who have or are at risk of developing BC-related lymphedema [35,37].

### Limitations

The majority of the available literature currently focuses on the most prevalent early stages of BC. Further research is needed to address a broader range of tumor types and to enhance the specificity of findings within the exercise oncology field. The limited number of trials directly comparing 2 or more levels of exercise training restricts understanding of dose-response relationships. Additionally, the lack of sufficient evidence regarding cognitive impairment outcomes highlights a clear knowledge gap.

Literature is scarce on the application of strategies and techniques for cognitive rehabilitation in managing CICI symptoms. Only a few studies have investigated interventions targeting memory, attention, information processing, and executive function in individuals with CICI. Moreover, there is no evidence regarding the role of physical therapy interventions and their outcomes in enhancing cognitive function. However, substantial evidence supports the positive effects of exercise on cognitive function in various clinical populations, including older adults. In cancer populations, where cognitive function is a primary outcome, further research is warranted. Cognitive function is commonly assessed using both self-reported measures and neuropsychological tests.

### Future Direction

The data on the prevalence rates of cognitive impairment in cancer survivors after chemotherapy accounted for variables such as age and time since therapy termination. Subgroup analyses and meta-regression were used to examine potential influences on prevalence estimates. The criteria for performing meta-regression were derived from Cochrane Guidance 35 [38]. A comprehensive meta-analysis was used to conduct the meta-regression. This review represents the first systematic comparison of prevalence rates of cognitive impairment in women with BC that has considered all methods used to ascertain impairment and evaluate long-term prevalence. Mean prevalence rates for CICI across all time points were 44% based on self-reports and 6% based on short cognitive screening [39]. The cognitive training intervention appears effective and may help reduce the deterioration of cognitive function in patients with CICIs.

### Conclusion

This RCT aims to provide a comprehensive rehabilitation strategy that simultaneously addresses physical and cognitive issues. Outcome measures such as the MMSE, Montreal Cognitive Assessment, Functional Assessment of Cancer Therapy-Cognitive, EORTC QLQ-C36, and the Patient-Specific Functional Scale will be used to evaluate the efficacy of the protocol. It is crucial to consider several challenges and limitations, including variability in patient responses, adherence to guidelines, and the need for skilled health care professionals to deliver the treatments consistently. Furthermore, a robust RCT with an adequate sample size and an appropriate control group is essential to establish the protocol’s effectiveness and generalizability in treating CICI.

